### Experimental intervention

2.6

ROOMMATE I. In phase 2, the VRRS1 will be enriched with digital educational and rehabilitation contents developed by a multidisciplinary team, following the collection of stroke stakeholders’ needs. The digital content will provide general knowledge about the pathogenesis and prognosis of stroke, and strategies and advice for self-management and/or caregiver-assisted management of the condition. It will also include practical information about the daily therapy scheduling and profiles of all health professionals involved in patient care. The rehabilitation content will include system-guided motor and cognitive exercises that the patient can perform independently or with the help/supervision of their family member or caregiver. The wide range of digital content (pre-existing VRRS features and new educational/rehabilitation content) will be customized by the therapists, based on the specific rehabilitation objectives.

ROOMMATE II. In phase 3, the VRR1 will be integrated with the BM4ROOMMATE system, developed by the University of Florence to provide and integrated system VRRS2. The BM4ROOMMATE is composed of (i) a set of Inertial Measurement Units (IMUs) that should be placed on the hand. (ii) a custom interface to manage the data acquisition and (iii) custom algorithms to measure patients’ performance on a selected set of exercises (e.g., velocity, IAV, number of repetitions). BMR4ROOMMATE is connected through Bluetooth to Khymeia platform so this data can be also visualized from the clinician, if necessary. The measures derived from BMR4ROOMMATE will be used to monitor motor recovery and to assist clinicians in evaluating and objectifying motor performance. All end users will have access 7 days a week to the system’s functionalities and digital contents. The therapists will indicate to the patients and/or their families the most suitable content according to patients’ clinical status. The e-HC will be available in person 5 days a week to train stroke survivors and caregivers and empower them to make independent use of the proposed technologies. In each phase, the intervention will last 3 weeks.

The description of the intervention according to the Template for Intervention Description and Replication (TIDIER) (22) checklist is provided in Supplementary material.

### Control intervention

2.7

All participants will receive UC, meaning they will be involved in the usual stroke rehabilitation pathway, undergoing the individual rehabilitation project, personalized based on needs and adapted according to the severity of the deficits, energy reserve, degree of frailty, and the main objectives of the rehabilitation program. The UC pathway has been developed in reference to the American Heart/America Stroke Association (AHA/ASA) (4), European Stroke Organization (23), and Italian stroke prevention and educational awareness diffusion (SPREAD) guidelines (24). Both guidelines emphasize intensive interdisciplinary rehabilitation and the Italian guideline specifies that this means at least 3 h of specific rehabilitation per day, including all specific motor and cognitive interventions. UC includes physiotherapy, OT interventions for activities of daily living (ADL) training, pharmacological interventions and nursing care, as well as, according to individual needs, cognitive assessment and training, deglutition, speech and language assessment and training, and psychological support to patient and family. Care is individually tailored to patient’s needs and to the type and severity degree of the identified functional deficits and activity limitations, and to the objectives of the rehabilitation program. Including comorbidities, also intervening on risk factors to prevent complications, recurrences or onset of new diseases.

### Outcome and assessment points

2.8

Participants will undergo a baseline (T0) and a post-treatment (T1) multidimensional assessment based on the Minimal Assessment Protocol for Stroke rehabilitation (PMIC2020) developed by the Stroke Section of the Italian Physical and Rehabilitation Medicine Association (25). PMIC2020 will be integrated with recommended in-depth assessment of some dimensions such as motricity (26) and cognitive status (27). At T0, demographic (sex, age, education) and clinical (type of stroke, time since stroke, lesion laterality) variables will also be collected in addition to primary and secondary clinical outcomes, whereas T1 assessment will include all primary and secondary clinical outcomes and user experience, usability, feasibility and social impact measures.

For both RCTs, the primary outcome will be the independence in basic daily activities, measured by the modified Barthel Index (mBI) with a score 0–100, because it is a clinically meaningful goal for patients, healthcare professionals and healthcare systems, to which various rehabilitation interventions contribute.

Primary outcome measure: the modified Barthel Index (mBI) was selected to assess the level of disability, using a score from 0 to 100 (28).Secondary clinical outcome measures:Motor outcomes:to measure manual dexterity the 9-Hole Peg Test (9-HPT) was selected, with a score based on the total number of seconds taken by the subject to complete the test (29)the Fugl-Meyer Assessment scale, upper-limb section (FMA-UL), which evaluates senso-motor recovery with a score ranging 0–66 (26, 30);the Action Research Arm Test (ARAT) which evaluates upper limb function, with a score from 0 to 57 points (31).the Motricity Index (MI) which evaluates upper and lower limb muscle strength with a score from 0 to 100 (32).the Functional Ambulation Category (FAC) which evaluates the level of independence in ambulation with a score from 0 to 5 (33)Sensors based metrics of motor performance of the upper limb, derived both from Khymeia and from DIEF sensors (only in ROMMATE 2^nd^).Cognitive outcomes:Montreal Cognitive Assessment (MoCA) which evaluates cognitive function with score from 0 to 30 (27);the Hearth Test (HT) of the Oxford Cognitive Screen (OCS) which evaluates allocentric and egocentric neglect (34)the Hospital Anxiety and Depression Scale (HADS), which evaluates anxiety and depression using a score 0–21 (35).Quality of life:the Short Form-12 (SF-12), which evaluates health-related quality of life with a score range from 0 to 100 (36).

Additional secondary outcomes will be related to user experience, usability and feasibility, which will provide insight into the safety, acceptability, and scalability of the intervention, essential elements for real-world implementation:

User’s experience:the Training Evaluation Inventory (TEI) which evaluates the effectiveness of the training to the use of technology (37);the Unified theory of acceptance and use of technology (UTAUT) and the Digital Adoption Questionnaire which evaluate the perceived usefulness, perceived ease of use, and user acceptance (38, 39);Numerical Rating Scale (NRS 0–10) which evaluates the overall patient and caregiver satisfaction with the rehabilitation experience.Usability:the eHealth UsaBility Benchmarking Instrument (HUBBI) which evaluates the usability of products (40)the Wearability questionnaire which evaluates the user experience and satisfaction with BM4ROOMMATE system (only in ROOMMATE 2^nd^) (41).Feasibility:The number and kind of side effects and technology failure will be recorded to assess the feasibility of the VRRS supported treatment.

In cases where patients will not be able to use the system independently, the user’s experience and usability outcomes will be also assessed by their caregivers.

### Sample size estimation and data analysis

2.9

We estimated the sample size for the first RCT (ROOMMATE 1, phase 2) based on the primary outcome (mBI). A previous RCT (13) tested the effectiveness of an enriched environmental activities program compared to UC in an inpatient neurorehabilitation unit and found an effect size equal to about 0.25, as measured by the motor section of the Functional Independence Measure. This scale assesses the same domain as the mBI (i.e., independence in basic ADL). We hypothesize that the intervention proposed in ROOMMATE might have a larger effect, since we will develop ad-hoc infotainments and rehabilitation contents that will be available bedside throughout the day and that will involve informal and formal caregivers as well. Thus, considering a medium effect size (0.5), a power of 0.80 and an alpha error of 0.05, we estimated a minimum sample size equal to 64 for each group, increased to 70 to account for a 10% drop-out rate. In the second RCT we planned to enroll 60 patients in total in the two participating clinical centres, an adequate sample for pilot studies according to Pearson et al., 2020 (42).

The Shapiro–Wilk test (*p* < 0.05) will be preliminarily used to check the data distribution. Continuous variables will be summarize as mean (SD) or median [IQR], as appropriate, and categorical variables as frequencies or percentages. Primary analysis metric is the difference in change from baseline between groups. For all variables, parametric (repeated measures 2 × 2 ANOVA) or non-parametric (Mann–Whitney test, Wilcoxon test) statistics will be used depending on the distribution of the data to detect within- and between-group differences over time. In addition, the proportion of participants showing changes greater than the estimated MCID for each outcome measure, when available, will be analysed using the chi squared test. All analyses will follow the intention-to-treat principle. Significance will be set at *p* < 0.05 in all analyses.

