
In Phase 2 and Phase 3, the digital system developed in phase 1 will be tested and compared to UC. Two slightly different technologies assemblies, named VRRS1 and VRRS2, both aimed at building a technology supported enriched environment, will be studied in succession. VRRS1 includes all the motor, cognitive and speech therapeutic modalities embedded in the original VRRS plus the informative and rehabilitation contents co-created in the first phase of the project; VRRS 2 includes all the features of VRRS1, that will be integrated to the BMR4ROOMMATE devices, providing a specifically developed sensorized motor assessment of the upper limb.

In phase 2, the VRRS1 will be tested in a randomized controlled trial enrolling a dynamic cohort of 140 participants, by a competitive recruitment in the two Clinical Centres (FDG in Florence, EUEH in Bucharest) through the systematic assessment for eligibility of all patients addressed to either centre for post-stroke inpatient rehabilitation. Eligible patients who will sign the informed consent will be consecutively recruited in either centre. Half of them will be randomly assigned to be proposed to receive the intervention VRRS1 in addition to usual care, and to be enrolled after signing another informed consent, while the other 70 will serve as controls, receiving only usual care. This first RCT is called ROOMMATE 1rst. In parallel to phase 2, the technical partners will carry out the integration of the VRRS with the MB4ROOMMATE inertial sensor.

At the end of phase 2, in both Clinical Centres the cmRCT recruitment will continue as before to enroll a dynamic cohort of at least 60 subjects in total; half of them will be randomly extracted to be proposed to participate in a pilot RCT (ROOMMATE 2nd) to study the effects of the integrated system VRRS2 (phase 3), and enrolled if providing informed consent, while the other 30 will serve as controls receiving usual care.

The VRRS system includes the proprietary content developed by Khymeia, consisting in a structured set of motor and cognitive exercises, each targeting specific rehabilitation objectives:

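### The 80% power stated for ROOMMATE 1st makes no allowance for patients who refuse the offer of VRRS1, although the offer is what is randomised and analysis is by intention to treat

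*Protocol article*

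**What the plan says.** Section 2.9 of the protocol article sizes ROOMMATE 1st on the modified Barthel Index, "considering a medium effect size (0.5), a power of 0.80 and an alpha error of 0.05". From these inputs, "we estimated a minimum sample size equal to 64 for each group, increased to 70 to account for a 10% drop-out rate". On the analysis set, the same section says "All analyses will follow the intention-to-treat principle".

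Section 2.5 (Procedure, the paragraph on phase 2) describes allocation among 140 consenting cohort members: "Half of them will be randomly assigned to be proposed to receive the intervention VRRS1 in addition to usual care". Patients allocated to the offer enter the intervention only once they have given a second, separate consent, so the offer can be declined. The comparison arm is the remaining half of the 140, of whom section 2.5 says "while the other 70 will serve as controls, receiving only usual care". The Introduction describes the cohort multiple RCT in the same way: randomly selected patients are offered the intervention, and their outcomes are compared with those of eligible patients who were not selected.

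Section 2.9 gives no expected acceptance rate and does not mention refusal.

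**The concern.** In this design consent to the intervention comes after randomisation, so a patient can be allocated to VRRS1 and then decline it. Under intention to treat that patient still counts in the VRRS1 arm while receiving usual care only. If the offer alone does nothing, each refusal pulls the arm difference towards zero.

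A dropout allowance does not correct this. It replaces outcomes that are lost; it does not restore an effect diluted by patients whose outcomes are kept. The power statement deals with the first problem and is silent on the second, which comes with the chosen design.

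What is at stake is how a null result is read. With 80% power on record, a non-significant difference would be taken as fairly strong evidence against a medium effect in patients who use the system. If a noticeable share refuse, that evidence is weaker than the article implies.

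**Working it through.** **Inputs from the article:** standardised effect 0.5, power 0.80, alpha 0.05, 64 raised to 70 per arm, dropout 10% (section 2.9); 1:1 allocation of the offer (section 2.5). The article does not state sidedness; a two-sided test reproduces its figure (one-sided would need about 50 per arm).

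**Inputs assumed:** acceptance of 100% down to 70%; decliners receive usual care and gain nothing from the offer; the standard deviation is unchanged by the mixture of accepters and decliners.

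**Step 1: reproduce the stated size.** The normal approximation is n = 2(1.960 + 0.842)² / 0.5² = 62.8, so 63 per arm. The two-sample t-test gives 63.77, so 64. The stated 64 is reproduced.

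**Step 2: patients analysed.** With no outcome loss, 70 per arm are analysed. With the planned 10% loss, 70 × 0.9 = 63.

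**Step 3: dilution.** Intention-to-treat effect = acceptance × 0.5.

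**Step 4: power.** Two-sample t-test, two-sided 0.05, at the diluted effect:

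| Acceptance (assumed) | Diluted effect | Power, 70 analysed | Power, 63 analysed |
|---|---|---|---|
| 100% | 0.500 | 83.6% | 79.5% |
| 95% | 0.475 | 79.7% | 75.3% |
| 90% | 0.450 | 75.3% | 70.7% |
| 80% | 0.400 | 65.2% | 60.6% |
| 70% | 0.350 | 53.8% | 49.6% |

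Hand check of one cell by the normal approximation, at 80% acceptance and 70 analysed: 0.4 × √(70/2) = 2.366; 2.366 − 1.960 = 0.406; power = Φ(0.406), about 65.8%. The t-test gives 65.2%.

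**Step 5: break-even.** With 70 analysed, the effect detectable with 80% power is about 0.477, so acceptance must be at least 0.477 / 0.5, or about 95%. With 63 analysed, the detectable effect is 0.503, already slightly above 0.5, so there is no room for any refusal.

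**Side note on dropout.** 64 / 0.9 = 71.1, which rounds up to 72, whereas 70 × 0.9 = 63. The difference is worth about 0.6 of a power point (80.1% against 79.5%), and 63 / 0.9 is exactly 70 if one starts from the normal approximation. This is a rounding matter and no part of the point.

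**The case against.** The strongest reply is that the loss is conditional. The article gives no acceptance rate, and some features favour a high one: willingness to take part and ability to use the devices, alone or with a caregiver, are inclusion criteria (section 2.3), and cohort members agree in advance to be approached about interventions (Introduction). This stands as a limit on the size of the problem. It does not remove it, because the second consent in section 2.5 keeps refusal possible, and section 2.9 does not say that refusal is expected to be negligible.

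Second, 0.5 might be meant as the effect of the offer. Section 2.9 does not say. Its reason for expecting more than the earlier trial's 0.25 is tailored content at the bedside all day and the involvement of caregivers, which reads more naturally as an effect of receiving VRRS1. If the offer was meant, the effect implied in recipients is 0.5 / 0.9 = 0.56 at 90% acceptance and 0.5 / 0.7 = 0.71 at 70%, and that should be stated.

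Third, the 70 might be accepters. The Abstract speaks of VRRS1 being both offered to and tested with 70 people, and section 2.5 ties enrolment to the second consent. The table would not then apply, but another difficulty would arise: decliners would be left out after randomisation, against the intention-to-treat rule, or replaced, against the even split of 140.

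Fourth, the 10% need not all be lost, since section 2.10 plans to collect outcomes after withdrawal and to use multiple imputation. This is fair, and is why the table also shows 70 analysed.

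A reader might go further and infer that the trial is underpowered, or that the sample size arithmetic is wrong. The documents support neither: without an acceptance rate no shortfall can be asserted as fact, and the 64 reproduces.

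**Conclusion.** The point holds as a gap in the assumptions behind the power statement. The stated 80% covers dropout only, while the design allows refusal after randomisation and the analysis keeps decliners in the offered arm.

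If 0.5 is the effect in recipients, the 70 are those offered, and decliners gain nothing from the offer, 80% power needs about 95% acceptance or more with complete outcomes, and full acceptance with the planned 10% loss. At 80% acceptance power would be about 61 to 65%, and at 70% about 50 to 54%. These acceptance rates are illustrations and not forecasts.

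The point does not invalidate the trial. It affects how much weight a null result can bear, and is worth correcting for that reason.

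**What to change.** Keep 140 patients and amend section 2.9, with a matching clarification in section 2.5:

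- State that the 70 are the patients offered VRRS1, and that those who decline stay in the offered arm under intention to treat.
- State whether 0.5 is the effect of the offer or of receiving VRRS1.
- Replace the single 80% figure with power across acceptance of 100/95/90/80/70%: about 84/80/75/65/54% with 70 analysed per arm and 80/75/71/61/50% with 63 analysed, marking the acceptance rates as assumptions.

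Any claim that baseline adjustment would recover some of the power should be added only with an assumed baseline correlation and the resulting figures.

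The cost is a few sentences and no further patients. The downside is that the stated power looks less favourable. Restoring 80% power by recruitment instead would, with 10% loss, need 88 per arm at 90% acceptance, 112 at 80% and 145 at 70%, so restating the power is the proportionate course.

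### A normality pre-test picks the primary mBI test, and the non-parametric branch does not say that it compares change from baseline

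*Protocol article*

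**What the plan says.** All of this stands in the protocol article, section 2.9 (Sample size estimation and data analysis), unless noted.

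- A Shapiro-Wilk test at p < 0.05 "will be preliminarily used to check the data distribution".
- The primary metric is declared to be the between-group difference in change from baseline.
- For every variable, the candidate tests are a 2 × 2 repeated-measures ANOVA, or Mann-Whitney and Wilcoxon. These "statistics will be used depending on the distribution of the data to detect within- and between-group differences over time".
- The sample size rests on "considering a medium effect size (0.5), a power of 0.80 and an alpha error of 0.05", and from this "we estimated a minimum sample size equal to 64 for each group, increased to 70 to account for a 10% drop-out rate".
- Section 2.8 (Outcome and assessment points) gives the primary outcome: "the modified Barthel Index (mBI) was selected to assess the level of disability, using a score from 0 to 100". It also fixes two assessments only: "Participants will undergo a baseline (T0) and a post-treatment (T1) multidimensional assessment".
- Section 2.10 (Monitoring plan and data management) adds sensitivity analyses and multiple imputation in general terms. Neither settles which test is primary.

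The article does not say whether Shapiro-Wilk is applied to raw scores, change scores or residuals, nor whether by arm or pooled. It does not say whether Mann-Whitney is applied to change or to T1 scores.

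**The concern.** The article states a rule for choosing the primary test, and the rule depends on the observed outcome data. Two analysts who follow it could run different primary tests on the same trial.

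The two branches are not equally well defined. With only T0 and T1, the group-by-time term of the ANOVA is exactly the comparison of mean change between arms, which is the declared metric. The other branch lists a between-group rank test without its input variable, and pairs it with a within-arm test. That pairing can be read as T1 compared between arms plus change tested within each arm. On that reading the between-arm test would no longer address change, and the planned power would not apply to it.

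The within-arm Wilcoxon test asks whether patients in one arm improved. Patients in subacute inpatient rehabilitation are expected to improve with or without the device, so a small p-value there says nothing about the intervention.

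**Working it through.** **Inputs from the article.** d = 0.5, power 0.80, alpha 0.05, 64 evaluable per arm, 1:1 allocation, mBI bounded at 0–100, two time points.

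**Assumptions, because the article is silent.** Two-sided testing; d = 0.5 on the scale of the SD of change; equal SD at T0 and T1; correlation r between T0 and T1 from 0.3 to 0.9.

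**1. The plan's own figure.** A two-sided two-sample t-test with d = 0.5 needs 63.77 per arm, so 64, and power at 64 is 0.801. (A one-sided test would give 50 per arm, so two-sided is the reading that fits.) The stated 64 is reproduced, and it belongs to a comparison of means.

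**2. Power of each possible primary test at 64 per arm.** In units of the raw-score SD, the SD of change is √(2(1 − r)), so the true effect is 0.5 × √(2(1 − r)).

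- *Change, t-test or ANOVA interaction:* standardised effect 0.5 for any r.
- *T1 scores:* standardised effect 0.5 × √(2(1 − r)).
- *ANCOVA:* residual SD √(1 − r²), so standardised effect 0.5 × √(2(1 − r)/(1 − r²)) = 0.5 × √(2/(1 + r)).

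The two Mann-Whitney columns come from 10,000 simulated bivariate normal trials per row. The other two are from the t-test power formula.

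| r | Effect on T1 | Change t-test | Mann-Whitney on change | Mann-Whitney on T1 | ANCOVA |
|---|---|---|---|---|---|
| 0.3 | 0.592 | 0.80 | 0.78 | 0.91 | 0.94 |
| 0.5 | 0.500 | 0.80 | 0.78 | 0.78 | 0.90 |
| 0.6 | 0.447 | 0.80 | 0.78 | 0.69 | 0.88 |
| 0.7 | 0.387 | 0.80 | 0.78 | 0.57 | 0.86 |
| 0.8 | 0.316 | 0.80 | 0.78 | 0.41 | 0.84 |
| 0.9 | 0.224 | 0.80 | 0.78 | 0.23 | 0.82 |

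Example at r = 0.8: the effect on T1 is 0.5 × √0.4 = 0.316, and the ANCOVA effect is 0.5 × √(2/1.8) = 0.527.

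**3. How often the pre-test would switch branch.** Scores were simulated as rounded values bounded at 0–100, 64 per arm, with assumed SD 25, baseline mean 30–50, mean gain 20–25 and r = 0.7 or 0.8 (2,000 trials per setting).

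- Shapiro-Wilk on raw scores rejects in at least one arm or time point in about 56–100% of trials. Under other assumed settings (baseline mean 35–55, SD 15–25) it was as low as about 15%.
- Shapiro-Wilk on change scores rejects in at least one arm in about 9–12%.

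So the variable being pre-tested, which the article does not name, largely decides the branch.

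**4. Harm from the pre-test when everything is done on change.** In the same simulations, choosing between the t-test and Mann-Whitney on change gave a type I error of 0.050–0.055. It cost at most about 0.4 points of power against always using the t-test.

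**5. Disagreement between branches.** In simulations of bounded scores with a true effect, the t-test and Mann-Whitney, both on change, gave opposite verdicts in 5–7% of trials. The change t-test and Mann-Whitney on T1 did so in 48–51%, in settings where r is well above 0.5.

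**The case against.** The sentence just before the list of tests names the difference in change between groups as the primary metric. With two time points, the natural rank counterpart is Mann-Whitney on change, which answers the same between-group question. This is a strong point, and most of it stands. A reader might infer that the non-parametric branch has no test of change between arms. The article does not support that: it fails to state one, but its declared metric allows one.

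A reader might also infer that much power will be lost. That needs three things together: Mann-Whitney run on T1 scores, a T0–T1 correlation well above 0.5, and d = 0.5 meant on the change scale. The article gives neither the correlation nor the scale of d. Below r = 0.5 the T1 test gains power over the change analysis. If d = 0.5 is on the SD of T1 instead, Mann-Whitney on T1 has about 0.78.

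Nor can the non-parametric branch be called the likely one, since that depends on what Shapiro-Wilk is applied to.

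It can be said that such details belong in an analysis plan that is not shown. That would hold if the article were silent. Instead it states a data-dependent rule that covers the primary outcome, and that rule is what needs changing. Finally, nothing in the article says that within-arm p-values will be used to claim efficacy. They are listed as inferential tests, so the risk is one of misuse.

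**Conclusion.** The point holds in limited form. Section 2.9 lets the observed distribution choose the primary mBI test, so no single primary analysis is fixed, and the non-parametric branch does not state that it compares change.

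If Mann-Whitney is run on change, the loss is about 2 points of power under normality (0.78 against 0.80), or about 1 to 4 points in the simulated bounded scores. The pre-test itself then does little harm. If it is run on T1 scores, power ranges from about 0.91 at r = 0.3 to 0.23 at r = 0.9, so the effect is a range that includes a gain. These figures assume d = 0.5 on the change scale, 64 per arm and two-sided testing. The correlation and the mBI distribution are assumptions, not figures from the article.

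The within-arm Wilcoxon test is no evidence about the intervention under any of these assumptions.

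**What to change.** In section 2.9:

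1. Remove Shapiro-Wilk as the selector of the test. It may stay as a guide to descriptive summaries.
2. Pre-specify one primary analysis whatever the distribution: ANCOVA of T1 mBI on arm and baseline mBI, with a heteroscedasticity-robust or bootstrap confidence interval. With two time points, its arm effect estimates the baseline-adjusted difference between groups in change. Under bivariate normality with d = 0.5 on the change scale, power is about 0.82 at r = 0.9 and 0.90 at r = 0.5, against 0.80 for the change analysis. The gain is smaller for bounded scores.
3. Name one rank-based analysis of change as a sensitivity analysis.
4. Report within-arm changes descriptively, and do not use their p-values as evidence of efficacy.

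The cost is a few sentences. No extra data or patients are needed, since baseline and T1 mBI are already collected. The change should be made before any outcome data are analysed.
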